### Study population

*Inclusion criteria for participants* will be as follows: family and community medicine and nursing residents; family doctors; and primary care nurses with assigned quotas.

*Exclusion criteria* will be: not having online gaming devices; not being able to follow up for 6 months; being an STI referral professional (STI referrers are those professionals who, after specific training, are designated as consultants with or without their own STI agenda).

## Statistical analysis

### Calculation of sample size

The sample size was determined based on findings from a pilot test involving pre- and post-intervention assessments conducted on 35 health professionals. Using the mean intervention effect (the mean test score improvement) and its standard deviation to estimate the expected intervention effect and within-group variability in the pilot test, the mean improvement was 2.07, with a standard deviation of 4.07. Assuming an alpha error of 0.05, a beta error of 0.2, and a design effect factor of 2 and expecting a 20% loss to follow-up after a 6-month period, the required sample size would be 262 (131 per group).In addition, the proportion of the LGTBIQ + population was considered to carry out a subsequent analysis from a gender and LGTBIQ + perspective. To estimate the proportion of LGTBIQ + professionals, data from the IPSOS (DeSilets et al. (DeSilets et al. [22])) survey were used; 14% of the Spanish population is estimated to belong to this group. This is the same proportion obtained in the sample of the pilot test (5 individuals (14.29% of the 35 participants) identified as LGTBIQ + ..

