## Data collection and sources of information

The participants in each group will complete an initial knowledge test. Once the first knowledge test will be completed, the participants in the intervention group will carry out the training activity, and at the end of the activity, they will answer the knowledge test again and complete a satisfaction survey on the same platform. The control group will not complete these post-intervention questionnaires. After 3 months, the knowledge test will be repeated for both the intervention and control groups. The data will be collected and stored in the same way.

Clinical data (request for tests, recording of health problems and antibiotic prescriptions) will be extracted from the computerized medical records.

Data from epidemiological surveys of notifiable diseases will be requested from the Public Health Agency.

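### The sample size treats an uncontrolled pilot pre-post gain as the between-arm effect, and 262 does not give the stated 80% power for that effect in an unadjusted two-sided comparison

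*Protocol article*

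**What the plan says.** The protocol article, under Calculation of sample size, bases the figure on "a pilot test involving pre- and post-intervention assessments conducted on 35 health professionals". It reports that "the mean improvement was 2.07, with a standard deviation of 4.07" and describes the step from pilot to trial as "Using the mean intervention effect (the mean test score improvement) and its standard deviation to estimate the expected intervention effect". For the error rates and clustering the inputs are "Assuming an alpha error of 0.05, a beta error of 0.2, and a design effect factor of 2". For attrition, the section writes of "expecting a 20% loss to follow-up after a 6-month period". The result, as the section gives it, is 262 participants, 131 in each arm. Nothing is deducted for change in controls or for loss of knowledge over time.

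On timing, Data collection and sources of information says that controls skip the immediate post-test, and then: "After 3 months, the knowledge test will be repeated for both the intervention and control groups". The Methods section also has controls tested at baseline and 3 months. The abstract differs: it puts controls on the same time sequence as the intervention arm. The Discussion expects better results in intervention participants than in controls, so a between-arm comparison is intended.

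**The concern.** A pre-post gain in one group mixes the effect of the game with anything else that raises a second score, such as having seen the test before. The trial will estimate the intervention gain minus the control gain. Using the whole pilot gain as the effect sets the control gain to zero without saying so. The article has reason to doubt that: controls sit the test at least twice, and the Limitations section relies on controls to offset the influence of being assessed.

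Timing may add to this. On the Methods and Data collection text, 3 months is the only time after baseline at which both arms are tested. If the pilot post-test came straight after the game, the calculation also assumes full retention.

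At stake is how a null result will be read. Against a claimed 80% power it looks like evidence of no worthwhile effect. If the power for the contrast actually made is lower, it is much weaker evidence.

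**Working it through.** **Inputs**, all from Calculation of sample size: difference 2.07; SD 4.07; alpha 0.05 (taken as two-sided, since sidedness is not stated); power 0.80; design effect 2; loss 20%; 131 per group.

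**1. The plan's own figure.** Per arm, before inflation:

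n = 2 × [4.07 × (1.960 + 0.842) / 2.07]² = 60.7

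Times design effect 2: 121.4. Divided by 0.8: 151.7 per arm. Rounding once at the end gives 152 per arm, 304 in total. Rounding at each step (61, 122, 153) gives 306. Other routes also miss 131 per group:
- multiplying by 1.2 instead of dividing by 0.8: about 146 to 147;
- a t-based calculation: about 155;
- a one-sided test: 120;
- a paired formula: 76 to 81.

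**2. Power at 131 per group.** Effective n per arm = 131 × 0.8 / 2 = 52.4.

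Power = Φ(δ/SD × √(52.4/2) − 1.96)

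For δ = 2.07: 2.07/4.07 × 5.119 − 1.96 = 0.643, so power is 74%.

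Difference detectable with 80% power = 2.802 × 4.07 × √(2/52.4) = 2.23 points.

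**3. Smaller net differences.** The documents give no control gain and no retention figure, so these are assumptions. Examples:
- control gain 0.5: net 1.57, power 51%;
- 20% fading: net 2.07 × 0.8 = 1.656, power 55%;
- both: net 1.156, power 31%.

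**4. Effect of baseline adjustment.** Planned analysis names ANCOVA, tentatively. With equal variances before and after, the change score has variance 2σ²(1 − ρ) and the ANCOVA residual has σ²(1 − ρ²). The adjusted SD is therefore 4.07 × √((1 + ρ)/2): 3.75, 3.52 and 3.28 for ρ = 0.7, 0.5 and 0.3. No ρ is given, so these values are assumptions. The design effect is held at 2.

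| Net difference | Unadjusted | ρ = 0.7 | ρ = 0.5 | ρ = 0.3 |
|---|---|---|---|---|
| 2.07 | 74% | 81% | 85% | 90% |
| 2.0 | 71% | 78% | 83% | 88% |
| 1.75 | 60% | 67% | 72% | 78% |
| 1.5 | 47% | 53% | 59% | 65% |
| 1.0 | 24% | 28% | 31% | 34% |

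**5. Precision of the pilot gain.** 2.07 ± 2.032 × 4.07/√35 gives a 95% interval of 0.67 to 3.47.

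**The case against.** Several points on the other side have force.

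- **The fall from 80% to 74% is not caused by the uncontrolled pilot.** It would be the same had the pilot been a randomised comparison. It comes from 262 not following from its inputs. This stands, and the two defects should be kept apart.
- **Fading is an inference.** The pilot's post-test time is not given. Under the abstract's schedule an immediate between-arm comparison would exist, and fading would not bear on it. This stands. The control-gain argument holds under either schedule.
- **ANCOVA could offset the loss.** At 2.07 points it takes power to 81–90%, so power below 80% is not certain. At 1.75 the range is 67–78%, still short. The article says only that ANCOVA could be useful, so it cannot be counted on as the basis of the stated power.
- **The 20% loss is stated for 6 months**, whereas the shared knowledge test is at 3 months. With no loss at all, effective n is 65.5 and unadjusted power for 2.07 is 83%. A one-sided test also gives 83%. Neither is what the section states as its basis.
- **Retest gain need not cancel.** By month 3 the intervention arm has sat the test three times and controls twice, on the Data collection text. Some practice gain may stay in the contrast.
- **The pilot interval shows imprecision, not bias.** It reaches as far above 2.07 as below.

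A reader might infer that the trial is certainly underpowered, or that the pilot's design alone explains the shortfall. The documents support neither, since they give no control gain, retention, pilot timing or correlation. Nor is this merely detail left to a fuller document: the article states the effect, its source and the resulting number.

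**Conclusion.** The point holds in two separate parts.

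First, the stated effect is a single-group gain used as a between-arm difference. That is right only if controls gain nothing and, should the pilot post-test have been immediate, if nothing fades by 3 months. The direction of the error follows from any control gain or any fading. Its size cannot be read from the documents: unadjusted power of 60%, 47% and 24% belongs to assumed net differences of 1.75, 1.5 and 1.0. ANCOVA at assumed correlations softens the loss but at these differences does not restore 80%.

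Second, and independently, 262 does not follow from its inputs. About 304 to 306 are needed, so a full net 2.07 has about 74% power. This rests on a two-sided unadjusted comparison with design effect 2 and 20% loss.

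The passage is wrong as written and should be corrected. It does not by itself show that the trial must be enlarged.

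**What to change.** Reword the sample-size section and leave enrolment unchanged:

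- Define the target as the net between-arm difference in knowledge score at 3 months.
- Stop describing the single-group pilot gain as the expected between-arm effect, and state when the pilot post-test was done.
- State that 262 gives 80% power for about 2.23 points, and 74% for 2.07, in an unadjusted two-sided comparison with design effect 2 and 20% loss.
- Show power for net differences of 1.0 to 2.0, with and without baseline adjustment, giving the pre-post correlation assumed.
- Say that a null result will be interpreted by its confidence interval and the detectable difference.

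The cost is about a paragraph and a small table, and a less favourable stated power.

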**Methods/design:**

Multicentre cluster randomized controlled trial.

Groups of primary care professionals will receive an intervention (online video game on sex education and STIs [SEXIT]) and will be compared with control groups that will not receive the intervention. Group assignments will be randomized by clusters.

The study will consist of a pre-post evaluation of the intervention: a knowledge test will be administered before and after the intervention and 3 months after the intervention. This test will also be carried out on the same time sequence in the control groups. The impact of the training intervention will be assessed over a 6-month period, focusing on various variables associated with the clinical management of STIs. This evaluation entails the clinical records of diagnostic tests and antibiotic prescriptions related to the clinical approach to STIs.

The required sample size is 262 (131 per group).

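### The sample size of 262 (131 per group) does not follow from its own stated inputs, which require 304–306; at 262 the two-sided power is about 74%, not 80%

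*Protocol article*

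**What the plan says.** The section on calculation of sample size bases the figure on a pilot of 35 health professionals tested before and after the intervention, in which "the mean improvement was 2.07, with a standard deviation of 4.07". It then lists the design parameters, "Assuming an alpha error of 0.05, a beta error of 0.2, and a design effect factor of 2", and adds "expecting a 20% loss to follow-up after a 6-month period". From these it concludes that "the required sample size would be 262 (131 per group". The Methods/design part of the abstract carries the same number: "The required sample size is 262 (131 per group".

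The article does not say whether alpha is one- or two-sided, and it gives no formula or software. The Methods section describes a comparison of cluster-randomised intervention and control groups, so the relevant calculation is for two independent groups with equal allocation.

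**The concern.** Apart from sidedness, every input to a standard calculation is printed next to the result, so the result can be checked directly. When it is checked, 262 is too small for the inputs.

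This is the trial's headline design figure, and the abstract presents it as the required size. If it is wrong, the type II error of 0.2 is not what the design delivers. A non-significant result would then be credited with more power to detect 2.07 points than the trial had.

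**Working it through.** **Inputs** (all from the section on calculation of sample size): difference 2.07; SD 4.07; alpha 0.05, taken as two-sided by convention; power 0.80; design effect 2; loss 20%; allocation 1:1.

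**Attempt to reproduce the stated figure**

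- Unadjusted n per group = 2 × (1.960 + 0.8416)² × (4.07/2.07)² = 60.7
- Design effect: 60.7 × 2 = 121.4
- Loss: 121.4 / 0.8 = 151.7
- Total: 304. Rounding up at each step (61, 122, 153) gives 306.

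The stated 262 is about 14% below this (262/306 = 0.86; 262/304 = 0.86).

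**Other readings tried**

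| Reading | Per group | Total |
|---|---|---|
| Two-sided, normal, loss as /0.8 | 152–153 | 304–306 |
| Two-sided, t distribution, loss as /0.8 | 155 | 310 |
| Two-sided, normal, loss as ×1.2 | 146–147 | 292–294 |
| Two-sided, loss ignored | 122–124 | 244–248 |
| One-sided, loss as /0.8 | 120–123 | 240–246 |
| One-sided, loss as ×1.2 | 115–118 | 230–236 |
| Paired, two-sided, loss as /0.8 | 76–83 | 152–166 |
| **Stated** | **131** | **262** |

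Rounding in the printed 2.07 and 4.07 moves the two-sided normal result only between 153 and 155 per group. The closest approaches to 262 use an efficiency correction of 0.955 for a Wilcoxon test, which the article does not mention. Even then it must be combined with a one-sided alpha or with leaving out the stated 20% loss, and the totals are 256–260.

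**Working back from 131 per group.** With the other inputs held, 131 would need one of the following:

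- loss of about 7% (1 − 121.4/131 = 0.07) instead of 20%
- a design effect of about 1.73 (131 × 0.8 / 60.7) instead of 2
- an SD of about 3.78 (4.07 × √(52.4/60.7)) instead of 4.07

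Each of these contradicts a printed input.

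**Power at the stated size**

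- Effective n per group = 131 × 0.8 / 2 = 52.4, against 60.7 needed
- Noncentrality = (2.07/4.07) × √(52.4/2) = 2.603
- Two-sided power = Φ(2.603 − 1.960) = 0.740 (0.732 with the t distribution)
- Difference detectable with 80% power = 2.8016 × 4.07 × √(2/52.4) = 2.23 points
- If alpha were one-sided: Φ(2.603 − 1.645) = 0.831

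**The case against.** The strongest objection is that 74% is a conditional figure, not a fixed property of the trial. It assumes a two-sided test, an unadjusted comparison of change scores, exactly 20% loss and a design effect of exactly 2. A one-sided 0.05 test would have about 83% power at 262. That is correct, and the conditions should accompany the number. It does not rescue 262: a one-sided calculation requires only 240–246, and the article declares no one-sided test.

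The planned analysis also mentions ANCOVA and multilevel models, which could recover power. They are listed only as possibly useful or if applicable, and the sample size is built on the raw improvement. The gain also depends on a pre-post correlation that the article does not give (see the fix).

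The shortfall is modest: 6 percentage points of power, or 2.23 rather than 2.07 points on a 25-question test. The pilot estimate is itself imprecise. If all 35 people contributed, its 95% interval is 2.07 ± 2.03 × 4.07/√35, roughly 0.7 to 3.5. This limits the practical consequence but does not make the printed arithmetic right.

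Finally, the full protocol may record the formula or a further input. That is why it cannot be said here which element is wrong: the total, the loss, the design effect or something unreported. It cannot make 262 follow from the inputs as published.

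**Conclusion.** The concern holds. The stated inputs require 304–306 participants, not 262, and no standard formula applied to them gives 131 per group.

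At 262, power for 2.07 points is about 74% (73% with the t distribution), a type II error of about 26% rather than 20%. This rests on a two-sided 0.05 test, a change-score comparison, 20% loss and a design effect of 2. It also rests on the plan's own premise that the pilot's uncontrolled gain equals the between-group difference; any gain in controls would lower the power further.

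One side scenario, not needed for the conclusion: if only the 13 centres already marked as enrolled took part, a t test on about 11 between-cluster degrees of freedom would have about 66% power. Recruitment was still open and 46 centres are listed as invited, so this is an assumption, not an expectation.

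**What to change.** Reconcile the figure with its inputs in both the abstract and the section on calculation of sample size. Either:

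- give 304–306 as the size these inputs require; or
- keep 262 and state about 74% power for 2.07 points (80% for 2.23 points), with the test two-sided.

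In either case state the sidedness and give the steps in one line: unadjusted n, times the design effect, divided by 0.8. If a different loss, design effect or SD was actually used, print that value instead.

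A third route is to keep 262 and base the power on a committed baseline-adjusted analysis. If 4.07 is the SD of the change, ANCOVA multiplies the variance by (1 + r)/2, where r is the pre-post correlation. The article gives no r, so a range must be shown. With the design effect held at 2, power at 262 is:

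| r | Power |
|---|---|
| 0.5 | 85% |
| 0.7 | 81% |
| 0.8 | 78% |
| 0.9 | 76% |

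Power falls below 80% once r exceeds about 0.73, so this route should rest on the correlation observed in the pilot rather than on a convenient value.

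Restating the power costs wording in two places and a slightly less favourable figure, with no extra participants. Holding 80% power on the current basis costs 42–44 more participants (304 − 262 to 306 − 262).

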### Planned analysis

For the treatment and analysis of the data, a descriptive analysis of the variables (percentages and averages with measures of dispersion) will be carried out according to the nature of the variables.Demographic and background data: descriptive statistics will be used (mean, median, standard deviation, range) to summarize the characteristics of the participants, including age, sex, years worked, etc. The distribution of test scores will be used to observe the distribution of pre- and postintervention test scores.Sensitivity analysis of the instrument: Analyses will be repeated using different methods to verify the robustness of the results.Comparison of baselines – Mann‒Whitney U or independent sample T-tests: whether the groups will be comparable in terms of demographic characteristics and baseline scores. Chi-square tests will be used to compare categorical proportions between groups (if applicable).Analysis of the effect of the intervention: T-tests for dependent samples or Wilcoxon signed-rank tests will be used to compare pre- and postintervention values within the same group. ANCOVA (analysis of covariance): to control for confounding or baseline variables, ANCOVA could be useful. Mixed analysis of variance (ANOVA): for multiple repeated measures (for example, pre, post- and 3-month follow-up).Cluster analysis (if applicable): Multilevel analysis or mixed models. These models will be useful for considering the hierarchical nature of clusters in the data.Lost data management – sensitivity analysis: To determine if missing data affects the results. Imputation techniques such as multiple imputation could be used if there is a significant amount of missing data.

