## Methods

We will design, develop, and evaluate an educational intervention in the form of a video game aimed at primary care professionals. The intervention will be studied and compared with control groups that will not carry out the intervention.

Design: Design-cluster randomized clinical trial with pre-post evaluation. The PCC teams (health professionals working in a primary care centre (doctors, nurses and residents)) will be randomly assigned to the intervention or control group.

The intervention groups are doing a preintervention test, which will be repeated immediately after the intervention and then 3 months later. In the control groups, the test will be administered at the beginning of the study and repeated after 3 months. In addition to questions to assess knowledge, there will be a qualitative assessment satisfaction survey for the participants. This test will also be carried out at the same time in control groups with the same sociodemographic characteristics.

The intervention will consist of an online video game developed by a multidisciplinary team.

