## Discussion

We expect to obtain a validated educational tool that, through gamification, allows primary care professionals to increase their knowledge of sexuality, sexually transmitted infections, and the prevention and detection of violence, improving the results of the evaluation test after the educational intervention.

Expected results:An increase in the knowledge of sexuality, sexually transmitted infections, and the prevention and detection of violence among primary care professionals, as well as an improvement in the results of the evaluation test after the educational intervention and improved results in the participants of the intervention groups compared to their control groups.An increase in the number of diagnostic and screening tests performed after the intervention in comparison to the control group.A better recording of diagnoses and more appropriate antibiotic treatments for the groups of professionals for whom the intervention will be carried out.

The aim of this study is to evaluate the tool used by primary care professionals But in the near future it is expected to be possible to play the game at different levels of difficulty.. The level of difficulty will depend on the videogame players: professionals, university students of health sciences or patient populations as young people.

We expect to build an educational tool that motivates active participation and facilitates acquisition of knowledge and safe behaviours related to sexual health in the short and medium term, including the prevention and detection of violence based on gender, sexual identity or orientation, access to the health system, and prevention, detection, and treatment of sexually transmitted infections. Likewise, we expect this tool to be a facilitator of health education for at-risk or vulnerable groups.

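### The only effect test the plan commits to is a pre-post test within each group; no intervention-versus-control contrast is named among the methods listed

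*Protocol article*

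**What the plan says.** The Methods section sets up a comparison of randomised groups. Centre teams "will be randomly assigned to the intervention or control group", and "The intervention will be studied and compared with control groups that will not carry out the intervention". The expected results in the Discussion are in the same terms: "improved results in the participants of the intervention groups compared to their control groups".

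The Planned analysis section lists these methods:

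- **Effect of the intervention, committed:** "T-tests for dependent samples or Wilcoxon signed-rank tests will be used to compare pre- and postintervention values within the same group".
- **Effect of the intervention, optional:** "to control for confounding or baseline variables, ANCOVA could be useful".
- **Effect of the intervention, listed without a stated contrast:** "Mixed analysis of variance (ANOVA): for multiple repeated measures (for example, pre, post- and 3-month follow-up").
- **Clustering, conditional:** "Cluster analysis (if applicable): Multilevel analysis or mixed models".
- **Between-group tests, for baseline only:** independent-sample, Mann-Whitney and chi-square tests, to see "whether the groups will be comparable in terms of demographic characteristics and baseline scores".

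On timing, the design paragraph in Methods gives controls a test at the start and at 3 months. The Data collection section says outright that controls do not take the questionnaires that follow the game. The Abstract speaks of the same time sequence in controls, but the two more detailed sections agree that the arms share only baseline and 3 months.

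**The concern.** A paired test within one arm asks whether scores rose in that arm. Repeating the same 25-question test, or knowing that one is being assessed, can raise scores in both arms. Only a contrast between arms removes such shared gains, and that contrast is the reason for randomising centres. The Limitations section itself relies on the control comparison to reduce bias from participants knowing that they are assessed; a within-arm test gives up that protection.

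An analyst who follows only what the plan fixes would report a p-value for each arm. A significant rise with the game, or a rise significant in that arm and not in control, could then be presented as efficacy although no difference between arms had been tested. For the immediate post-test no control value exists at all, so any gain at that point is uncontrolled.

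**Working it through.** **The text.** Each listed method can be checked for whether it is fixed and whether it names an arm contrast on the knowledge score.

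| Method | Status | Arm contrast named? |
|---|---|---|
| Paired t or signed-rank | Committed | No, within group |
| ANCOVA | Optional | No |
| Mixed ANOVA | Listed | No; its example needs a time point that controls lack |
| Multilevel or mixed model | Conditional | No; described as handling hierarchy |
| Independent-sample tests | Committed | Yes, but for baseline comparability |

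The condition on the multilevel model is out of place: centres are the unit of randomisation, so clustering is certain by design.

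**Size of the risk.** The plan gives no figure for this point to reproduce. Inputs from the sample size section are the SD of pre-post change, 4.07; 131 per group; and 20% loss, so 131 × 0.8 = 104.8 analysed per arm. The 131 is taken as stated. Two assumptions are not in the documents: a two-sided 5% level (the plan gives 0.05 without sidedness) and a gain g shared by both arms with no effect of the game.

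Standard error of the mean change in one arm: 4.07/√104.8 = 0.398. With λ = g/0.398, the chance that an arm is significant is P = Φ(λ − 1.96) + Φ(−λ − 1.96). The chance that the intervention arm shows a significant gain and control is not significant is Φ(λ − 1.96) × (1 − P).

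| Shared gain g | λ | Intervention arm significant | Intervention significant, control not |
|---|---|---|---|
| 0 | 0 | 5% | 2.4% |
| 0.25 | 0.63 | 10% | 8% |
| 0.5 | 1.26 | 24% | 18% |
| 0.75 | 1.89 | 47% | 25% |
| 1.0 | 2.52 | 71% | 21% |

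The last column peaks at about 25% and then falls, because with a large shared gain control becomes significant too.

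**Sensitivity to clustering.** With the plan's design effect of 2 allowed for, the effective number is 104.8/2 = 52.4 and the standard error 4.07/√52.4 = 0.562. For g = 0.25, 0.5, 0.75 and 1.0, the intervention arm is significant 7%, 14%, 27% and 43% of the time, and intervention-only significance occurs 6%, 12%, 19% and 24% of the time. The rates are lower, but the conclusion is the same.

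**What baseline adjustment could add.** For a between-arm test of change scores with the pilot gain of 2.07 taken as the true difference: standard error 4.07 × √(2/52.4) = 0.795; 2.07/0.795 = 2.603; power Φ(2.603 − 1.96) = 74%. If pre and post scores have equal variance and correlation r, ANCOVA multiplies the variance by (1 + r)/2, so power is Φ(2.603/√((1 + r)/2) − 1.96).

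| r (assumed) | Variance factor | Power |
|---|---|---|
| 0.3 | 0.65 | 90% |
| 0.5 | 0.75 | 85% |
| 0.7 | 0.85 | 81% |
| 0.9 | 0.95 | 76% |

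**The case against.** The strongest reply is that the plan is not confined to within-arm tests. Mixed ANOVA stands in the same item with no conditional wording. Such a model ordinarily crosses time with a between-subject factor, and in a two-arm trial that factor would naturally be arm; it could be fitted to baseline and 3 months in both groups. A multilevel model could carry a treatment term as well. This stands. A reader might infer that no listed method could use the controls, and the documents do not support that. The defect is narrower: the one fixed test is within-group, and none of the alternatives is given the arm contrast.

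Two other inferences go too far. One is that the baseline comparability tests will decide whether ANCOVA is used; the plan lists them as a separate item and ties them to no choice of covariates. The other is that significance in one arm only is the planned decision rule. No such rule is stated, and the Abstract, Methods and Discussion all speak of comparison with controls. The misreading is one the analysis wording permits, not one it prescribes.

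It can also be said that a journal article leaves model detail to a fuller document. That holds for covariate lists and model options. It does not excuse the wording here, because the article itself assigns the effect analysis to within-group tests.

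Finally, the error rates depend on a shared gain for which the documents give no figure. That is correct, and is why they are shown as a range.

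**Conclusion.** The point holds and should be settled before analysis. The committed effect test does not estimate the intervention-versus-control difference that the trial is designed to show, and no other listed method is tied to that difference.

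The possible harm, with no true effect, is a within-arm false signal 10% to 71% of the time and an intervention-only signal 8% to 25% of the time, against a nominal 2.5% in the favourable direction. These figures rest on an assumed shared gain of 0.25 to 1.0 points, the pilot SD, 104.8 analysed per arm, a normal approximation and no allowance for clustering. They show what could follow from relying on the within-arm tests; they do not predict what the trial will report.

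The precision gain from ANCOVA is secondary. It ranges from about 90% to 76% power for r from 0.3 to 0.9, against 74% for a between-arm change-score test. Since the plan names no such change-score test, that difference does not measure a loss from the plan as written.

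**What to change.** State in the Planned analysis section that the effect of the intervention on knowledge is the between-arm difference in the 3-month score, adjusted for the baseline score in all cases, estimated in a mixed model with a random effect for centre and reported with a 95% CI. Remove the conditional wording on clustering.

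Report within-arm changes as descriptive only, including the immediate post-test in the intervention arm, and limit the three-time-point example to that arm. If a precision gain from baseline adjustment is quoted, give it as a range over the unknown pre-post correlation.

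This is a change of wording. It uses the baseline and 3-month tests already planned in both arms and needs no further data.
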